**Methods:**

Participants who demonstrate partial or full response to rTMS, defined as at least 25% reduction in symptoms, as quantified using the Inventory of Depressive Symptomatology–Self-Report (IDS-SR) or an IDS-SR score of 22 or lower will be included. Twenty participants will be randomly allocated to either face-to-face or online PCT, and treatment adherence will be compared between face-to-face and online treatment. The study will be deemed feasible if at least 75% of participants complete PCT during the grant duration of 1.5 years. For PCT, we aim to see which delivery format is the most feasible. Secondarily, changes in affective states, assessed through experience sampling data during PCT, will be studied to establish usefulness for a larger randomized controlled trial aimed at evaluating the effectiveness of PCT after rTMS. Finally, possible MDD relapse will be monitored throughout the intervention and follow-up periods.

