**Results:**

This study was funded in November 2023 by the Netherlands Organisation for Health Research and Development. It was reviewed and approved according to the Medical Research Involving Human Subjects Act (*Wet Medisch-Wetenschappelijk Onderzoek met Mensen*) by the Medical Research Ethics Committee of Amsterdam University Medical Center on June 17, 2024. Data collection started in August 2024 and ended in April 2026, with an inclusion of 11 participants. As of June 2026, data analysis has not yet started. We expect data analysis and manuscript preparation of results to be completed in December 2026.

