### Study Design

This study is a pragmatic monocenter RCT with a 1:1 parallel-group design. Twenty patients with MDD who (partially) responded to rTMS treatment will be randomized to either face-to-face or online PCT. This sample size was selected based on practical feasibility in terms of the number of patients with MDD receiving rTMS treatment in Amsterdam, the Netherlands. PCT will be offered as soon as possible after the last rTMS session. Throughout the course of PCT, all patients in both conditions will receive 8 weekly individual sessions (either online or in person) and will be asked to fill out a daily short-form questionnaire. Patients will be assessed before PCT (baseline), directly after PCT (after treatment), and 3 and 6 months after baseline. Total participation duration for the study will be approximately 6 months, as shown in Figure 1. Table 1 provides an overview of the study assessments.

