### Randomization and Blinding

In total, 20 participants will be randomized with a 1:1 allocation ratio to PCT online or face-to-face. A computer-generated randomization table with small block sizes stratified by gender will be used by an independent researcher. After randomization has taken place, an independent researcher (who is not blinded to treatment allocation and will not conduct outcome assessments) will contact the participants and related health care professionals to communicate the participants’ treatment allocation to start the PCT sessions. Participants will be instructed not to share treatment allocation with the blinded outcome assessor. This is to ensure that outcome assessors remain blinded until the end of data collection and consequent database lock.

If knowledge of the allocated group is necessary for the safety of the patients or providing medical treatment, unblinding will be performed by the treating psychologist or the previously mentioned independent researcher.

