#### Primary Outcome

Treatment adherence is the main study parameter and will be measured using registrations on presence during sessions and Epic electronic health records. Treatment adherence will encompass the number of PCT sessions followed, number of weeks in which treatment was administered, outcome rating scale of each PCT session [52], and adherence to homework assignments. Adherence to treatment will be promoted by related health care professionals. Feasibility measures of the different PCT formats will include the percentage of questionnaires completed. If there are significant differences in adherence and feasibility measures between the online and face-to-face PCT groups, this study will advise using the delivery format with the highest feasibility and treatment adherence for a larger RCT on efficacy. If there is no significant difference, then we will advise future RCTs to offer both methods and tailor the delivery format to the preference of the participant. The feasibility of the study itself will be based on recruitment and inclusion rate and number. The study itself will be defined as feasible if at least 75% of participants are able to complete PCT after rTMS within the duration of the grant (ie, 1.5 years).

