## Results

This study was funded in November 2023 by the Netherlands Organisation for Health Research and Development. Data collection started in August 2024. As of September 2025, participant recruitment has concluded with a total of 11 participants. In April 2026, the last follow-up measures were performed, and data collection ended. As of June 2026, data analysis has not started. We expect data analysis and publishing of results to be completed in the fall or winter of 2026. The study findings will be disseminated through publication in peer-reviewed scientific journals, as well as presentations at relevant platforms such as clinical care meetings where appropriate.

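### The 75% completion rule that labels the study feasible has no fixed denominator or grant window and no recruitment component, so the 11 of 20 enrolled can pass or cannot pass depending on the reading

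*Protocol article*

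**What the plan says.** Two consecutive sentences under Primary Outcome deal with the feasibility of the study, as distinct from that of the two delivery formats. The first gives its basis: "The feasibility of the study itself will be based on recruitment and inclusion rate and number". The second gives the rule: "The study itself will be defined as feasible if at least 75% of participants are able to complete PCT after rTMS within the duration"; the period meant is the grant's, stated as 1.5 years. The Methods part of the Abstract repeats only the rule: "The study will be deemed feasible if at least 75% of participants complete PCT during the grant duration of 1.5 years".

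The planned size appears under Randomization and Blinding: "In total, 20 participants will be randomized with a 1:1 allocation ratio". Study Design gives its basis: "This sample size was selected based on practical feasibility in terms of the number of patients with MDD receiving rTMS treatment in Amsterdam". The Results section reports what was achieved: "As of September 2025, participant recruitment has concluded with a total of 11 participants".

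Statistical Analysis of the Primary Objective says that recruitment and completion rates will be described qualitatively as indicators of study feasibility. The article sets no target or minimum for recruitment in judging feasibility. It gives the month of funding (November 2023) and of the start of data collection (August 2024), but not the dates on which the grant began and ended.

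**The concern.** The stated basis of the verdict and the stated rule for the verdict are different quantities. A share of participants who complete therapy does not depend on how many were recruited, unless the denominator is the planned number. The article does not say whether it is.

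This matters because enrolment is already known and is well below plan. If the denominator is those enrolled, the study can be called feasible although it recruited little more than half of its intended sample, and that sample was itself chosen as what local patient numbers would allow. If the denominator is the planned 20, the same data cannot meet the criterion. The undated grant window adds a second choice that can move individual completers in or out of the numerator. Unless both are settled before analysis, the reading can be chosen once the completion count is known.

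**Working it through.** **Inputs.** Planned N = 20 (Study Design; Randomization and Blinding). Enrolled = 11 (Results). Threshold = 75% within 1.5 years, that is 18 months (Primary Outcome; Abstract, Methods). Funding November 2023, data collection from August 2024, recruitment closed as of September 2025, last follow-up April 2026 (Results). PCT lasts 8 weeks and the final assessment is 6 months after baseline (Study Design). The planned N has no statistical derivation, so there is no figure of the plan's own to reproduce.

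**Denominator.** Minimum completers = 0.75 × n, rounded up.

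| Denominator | 0.75 × n | Completers needed | Possible with 11 enrolled? |
|---|---|---|---|
| 11 enrolled | 8.25 | 9 (9/11 = 81.8%; 8/11 = 72.7% fails) | Yes |
| 20 planned | 15 | 15 (15/20 = 75%) | No |

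On the enrolled reading the rule takes no account of sample size: 3 of 4 or 6 of 8 would also pass.

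**Recruitment.** 11/20 = 55% of plan. Nine completers would be 9/20 = 45% of the planned number. If recruitment ran from August 2024 to September 2025, about 13 months, the rate was 11/13 = 0.85 per month. Reaching 20 in the same time needed 20/13 = 1.54 per month.

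**Grant window.** November 2023 + 18 months = about May 2025. August 2024 + 18 months = about February 2026. The first date falls before recruitment was reported closed. With 8 weeks of therapy, anyone who started after about March 2025 could not finish inside that window. If the April 2026 visit was a scheduled 6-month assessment, that participant's baseline was in about October 2025 at the latest reckoning, which is after the first window closed and before the second did. On the enrolled reading the rule tolerates two non-completers (11 − 9 = 2). Three participants finishing after the window would therefore be enough to fail it (8/11). The article does not say how many finished when.

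**Precision (secondary).** The exact (Clopper-Pearson) 95% interval for 9/11 is 48.2% to 97.7%. If the true completion probability were 75%, the chance of 9 or more out of 11 would be 46%.

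**The case against.** The strongest defence is that the two sentences can be reconciled. In the Abstract the threshold comes soon after the planned 20 are mentioned, and under Primary Outcome it directly follows the sentence on recruitment. Read as 75% of the planned 20 within the grant, it combines recruitment and completion in one criterion. That reading is possible, so a reader who infers a flat contradiction goes too far. The enrolled reading is nevertheless the plainer one: the Results section calls the 11 participants, and Statistical Analysis includes all who were randomised. What stands is an ambiguity that reverses the verdict.

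Three further inferences are tempting and are not supported:

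- *That recruitment is ignored or concealed.* It is a planned descriptive indicator of feasibility, and the figure of 11 is stated in both the Abstract and the Results. It is absent from the decision rule, not from the report.
- *That the decision on the larger trial turns on the 75%.* Nothing in the article says so. The Abstract's conclusions link a larger trial to a preferred delivery format, and the advice under Primary Outcome depends on differences between formats. The rule confers a label and has no stated consequence for progression.
- *That the lack of a session count for completion, or of an interval, is a defect.* A condensed article may leave both to the full protocol or analysis plan, and the 8-session course gives completion a natural meaning.

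The full protocol may also state the grant dates. In that case the remedy is to copy them in.

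**Conclusion.** The point holds as an ambiguity in a stated decision threshold. On the plainer reading, 9 of 11 completers make the study feasible at 55% of planned enrolment. On the other reading 15 are needed and the criterion is already out of reach. The window is open by about nine months (May 2025 to February 2026), and the article does not show which end is right. It would be wrong to conclude that the study has already failed its own criterion, since that follows only if the planned 20 was meant.

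The verdict rests on two assumptions: that the 18 months could run from either of the two dated events, and that recruitment began with data collection. The denominator result needs neither. Severity is should-fix: this is a descriptively analysed pilot that discloses its enrolment, but the ambiguity affects what the study may say about its own feasibility.

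**What to change.** Make the change before analysis starts (the Results section says it had not begun as of June 2026), in both the Abstract and Primary Outcome:

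1. State the denominator originally intended for the 75%, and the actual start and end dates of the grant.
2. If the denominator is those enrolled, present the 75% result as completion (acceptability) of PCT among all 11 randomised participants. Do not call the study itself feasible on that result alone. Report recruitment beside it, as 11 of 20 with the monthly rate, as a separate feasibility result that fell short of plan.
3. If the planned 20 was intended, report the criterion as not met.
4. Label any recruitment threshold introduced now as post hoc, because enrolment is already known.

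An exact 95% confidence interval for the completion proportion would be a useful addition but is not essential to the correction.

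The cost is a few sentences and no new data. The drawback for the authors is a less favourable feasibility statement.

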**Objective:**

This study aims to establish the feasibility of 2 distinct forms of PCT (online and face-to-face) after intensive rTMS treatment for responding patients.

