**Conclusions:**

If this pilot study shows preferred feasibility of a specific format of PCT (either online or face-to-face) following rTMS treatment for depression, a larger-scale randomized controlled clinical trial may be performed to study the effects of PCT on remission duration, relapse rates, and affective states in remitted individuals with MDD after rTMS treatment using this preferred delivery format. This pilot will provide insights into the feasibility of face-to-face or online PCT after successful rTMS treatment in depression.

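### The 75% completion criterion is pooled over both formats and the format advice is only relative, so neither online nor face-to-face PCT is held to a completion level of its own

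*Protocol article*

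**What the plan says.** The Abstract (Objective) sets the aim at the level of the format: "This study aims to establish the feasibility of 2 distinct forms of PCT (online and face-to-face". The Objectives section adds that the comparison is meant to keep dropout low in a later, larger RCT.

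The Primary Outcome section then fixes two rules.

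- **Study rule.** "The study itself will be defined as feasible if at least 75% of participants are able to complete PCT after rTMS", within the 1.5-year grant. The Abstract (Methods) repeats it: "The study will be deemed feasible if at least 75% of participants complete PCT during the grant duration of 1.5 years". Neither sentence splits participants by format.
- **Format rule.** If adherence and feasibility measures differ significantly between the groups, "this study will advise using the delivery format with the highest feasibility and treatment adherence for a larger RCT on efficacy". If they do not, future RCTs are advised to offer both formats according to participant preference. Neither branch carries a minimum level.

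The Abstract (Conclusions) makes a larger trial conditional in the same relative way: "If this pilot study shows preferred feasibility of a specific format of PCT". The analysis section for the primary objective hypothesises no difference in adherence and plans qualitative description. It names no test and sets no completion level per format.

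**The concern.** The larger RCT would run in one format or in both, so it needs to know whether each format is completed often enough. The study rule cannot say, because format is not an input to it: a well-completed format can lift a poorly completed one over the pooled 75%. The format rule cannot say either, because it looks only at the difference, and with 10 or fewer participants per format a non-significant difference is weak evidence of similarity. Since no difference is the stated hypothesis, advising both is the branch the plan expects to follow. Taken together, the two rules can give a favourable study verdict and advice to use both formats when one of them lost 40% of its participants, which works against the aim of limiting dropout.

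This is not detail left to an analysis plan. Both rules and both branches are written out; the problem lies in how they are fixed.

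**Working it through.** **Inputs from the article**

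- Planned size, from Randomization and Blinding: "In total, 20 participants will be randomized with a 1:1 allocation ratio to PCT online or face-to-face", so 10 per format.
- Achieved size, from Results: "participant recruitment has concluded with a total of 11 participants". The split by format is not given.
- Basis of the sample size, from Study Design: "This sample size was selected based on practical feasibility in terms of the number of patients with MDD receiving rTMS treatment in Amsterdam". No alpha, power or effect size is stated, so there is no planning figure to reproduce.

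**Assumptions**

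- Significance means a two-sided Fisher exact test at 0.05 on completion (yes/no).
- With 11 participants, the denominator of the 75% is 11.
- The split of the 11 is 6/5 or 7/4.
- True completion rates are as stated in step 4.

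**Step 1. The criterion as counts.** 0.75 × 20 = 15 completers. 0.75 × 11 = 8.25, so 9 completers.

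**Step 2. A result at 10 + 10: 9/10 versus 6/10.**

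- Pooled: 15/20 = 75%, which meets the criterion.
- Fisher, with 15 completers fixed among 20: P(9 and 6) = C(10,9)·C(10,6)/C(20,15) = 10 × 210/15504 = 0.135, and P(10 and 5) = C(10,10)·C(10,5)/C(20,15) = 252/15504 = 0.016. One tail is 0.152; both tails give p = 0.30.
- Not significant, so both formats are advised. The weaker one stands at 60%, with a Clopper-Pearson 95% interval of 26% to 88%.

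Other results that meet the pooled criterion with one format below 75%:

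| Completers | Pooled | Fisher p | Advice |
|---|---|---|---|
| 10/10 vs 7/10 | 85% | 0.21 | both |
| 9/10 vs 7/10 | 80% | 0.58 | both |
| 8/10 vs 7/10 | 75% | 1.00 | both |
| 10/10 vs 6/10 | 80% | 0.087 | both |
| 9/10 vs 6/10 | 75% | 0.30 | both |
| 10/10 vs 5/10 | 75% | 0.033 | better format only |

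Only the last row drops the weaker format.

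**Step 3. The 11 recruited, 9 or more completers needed.** With 9 completers the number of arrangements is C(11,9) = 55.

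- Split 6/5: the most extreme result is 6/6 versus 3/5, p = C(6,6)·C(5,3)/55 = 10/55 = 0.18.
- Split 7/4: the most extreme result is 7/7 versus 2/4, p = C(7,7)·C(4,2)/55 = 6/55 = 0.11.
- With 10 or 11 completers the p-values are larger still.

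No result that meets the pooled criterion can be significant, so advising both follows automatically. For example, 6/6 versus 3/5 is 9/11 = 82% pooled, with one format at 60%.

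**Step 4. How often this happens at 10 + 10.** Sum Bin(a; 10, p1) × Bin(b; 10, p2) over all pairs with a + b ≥ 15, Fisher p ≥ 0.05, and a or b at most 7.

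| Assumed true completion | P(pooled criterion met) | P(met, both advised, one format observed below 75%) |
|---|---|---|
| 95% and 60% | 0.73 | 0.44 |
| 80% and 80% | 0.80 | 0.34 |

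The second row is the comparator: the same pattern is common by chance when neither format is poor.

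**The case against.** **The study rule passes judgement on the study, not on a format.** This is correct. A reader might infer that the 75% rule can declare a poor format feasible. The text does not support that: the rule concerns the study itself and sits beside recruitment and inclusion. A weaker format is advised only through the separate branch for no significant difference. The point rests on the two rules in combination.

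**The relative rule cannot pick a winner below 75% in a study that passes.** Also correct. A reader might cite 7/10 versus 1/10 (p = 0.02) as a case where a format at 70% is advised. Pooled, that is 8/20 = 40%, so the study fails its own criterion. The better format is never below the pooled rate, so a significant winner in a passing study is always at 75% or more. Only the branch that advises both is open to criticism.

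**The test is assumed.** The article applies significance to several measures, including sessions, weeks, outcome rating scale, homework and questionnaires, and names no test. Sessions attended might separate groups that completion does not. This limits the p-values but does not supply the missing minimum level.

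**The denominator is open.** If the 75% refers to the planned 20, 15 completers cannot be reached with 11 participants and the study cannot pass. The figures for 11 hold only if 11 is the denominator.

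**Results will be described by group anyway.** A low rate in one format would probably be visible, and offering formats by preference may not reproduce dropout seen under random allocation. That softens the consequence; the written advice rule still ignores the rate.

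**A hard cut per format would perform poorly.** This stands. If both formats are truly at 85%, both reach 8/10 only 67% of the time. The rule would also be set after data collection ended.

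**Conclusion.** The concern holds in a limited form. The only completion threshold is pooled, the format advice has no minimum level, and so the plan never asks whether either format reaches 75%, although its objective concerns both formats. Followed as written, the rules can call the study feasible and advise both formats when one was observed at 60%. With 11 participants split 6/5 or 7/4, a passing study always leads to advising both.

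The structural gap depends on no assumption. The p-values depend on Fisher's test at 0.05 on completion, and the result for 11 also on the split and the denominator. The 44% depends on chosen true rates of 95% and 60%, and should be read against the 34% that arises when both are 80%; it is not a measure of how often a truly poor format would be advised.

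The point should be dealt with before the analysis. It does not invalidate the data.

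**What to change.** In the Primary Outcome section:

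1. Report completion for each randomised format against the 75% benchmark, with its exact 95% interval. Keep the pooled figure as the study-level verdict.
2. Do not advise both formats from a non-significant difference alone. Base the advice on each format's own completion. Where a format is observed below 75%, say so, and do not recommend it without that qualification.
3. Treat 75% per format as a guide to be read with its interval, not as a hard pass/fail cut.
4. Label the change as made after data collection ended but before analysis. The article states that analysis had not started as of June 2026.

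Align the Abstract (Conclusions), so that a larger trial depends on how well a format was completed and not only on one being preferred.

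Cost: no new data are needed, since attendance is recorded and participants are assessed by intervention group. The intervals will be wide (6/10 gives 26% to 88%; 3/5 gives 15% to 95%), and the verdict may be less favourable than the pooled figure alone.

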#### Secondary Outcomes

Affect fluctuations are the second study parameter and will be measured using a daily short-form questionnaire (via ESM), including the visual analog mood scale and questions on positive and negative affect [53-55]. Participants will complete the daily questionnaire on their affective state during PCT, from which the mean affect score will be calculated. To increase compliance with the ESM questionnaires, 3 strategies will be used in this study. First, the days in which participants receive the ESM questionnaires will be fixed and customized to the preference of each participant in consultation with the outcome assessor. Second, reminders to fill out the ESM questionnaires will be sent via email when compliance is low. Third, patients will be instructed to complete the ESM questionnaires as quickly as possible to minimize retrospective memory distortion. Low-responding individuals will also be included in the analysis.

To determine the remission period, the number of weeks of remission will be monitored using the IDS-SR [56] and HDRS-17 [57]. Relapses will be identified by the treating therapist. Both questionnaires will be used for registering depressive symptoms and response rates to rTMS (treatment as usual) and administered directly after completing PCT and 3 and 6 months after baseline.

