## Introduction

### Background

In 2015, more than 300 million people experienced major depressive disorder (MDD) [1]. This number has increased in recent years, partly due to COVID-19 [2]. Furthermore, in the Global Burden of Disease study of 2023, depressive disorders were in the top 3 causes of years lived with disability [3]. Common treatment options for MDD include psychological and pharmacological interventions. However, approximately 30% to 55% of patients with MDD receiving treatment have treatment-resistant depression (TRD) and, thus, do not meet remission criteria [4,5]. In addition to treatment resistance, recurrence and relapse pose another challenge. Experiencing a depressive episode increases vulnerability to relapse (40%-90% of individuals with a depressive episode relapse), and this vulnerability only increases after multiple episodes of depression [6]. Research has shown that fluctuations in positive and negative affect, especially reductions in positive affect, can predict depressive symptomatology up to 6 months after remission [7]. Notably, the 1-item visual analog mood scale outperformed the widely used 17-item Hamilton Depression Rating Scale (HDRS-17) or Inventory of Depressive Symptomatology–Self-Report (IDS-SR) in predicting relapse over 2 years [8]. This suggests that measuring affect fluctuations using experience sampling methodology (ESM) may be useful in predicting relapse after remission and may help assess the effectiveness of relapse prevention strategies.

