### Objectives

On the basis of these previous studies, the primary objective of this pilot study is to compare feasibility and adherence to treatment between online and face-to-face PCT to minimize dropout in a larger RCT. Secondary objectives are to explore the effects of offering PCT to patients who (partially) responded to rTMS treatment on affect fluctuations and remission periods, and study the potential benefits of these measurements for a larger trial.

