#### Statistical Analysis of the Secondary Objectives

To explore changes in affect fluctuations and the duration of a remission period, several statistical methods will be used. Repeated linear mixed models will be used if normality is reached to compare variation in individuals’ affective states over time in the intervention groups. Participants will be included as a random intercept. If applicable, demographic characteristics such as sex and age will be used as covariates. A survival analysis (ie, Kaplan-Meier curve) will be used to compare the time to depressive relapse (as assessed using the IDS-SR and HDRS-17) overall and between the 2 study groups. Finally, to identify the optimal course of therapy in a larger future RCT, the descriptive results of the secondary parameters will be qualitatively illustrated.

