rTMS as a treatment for MDD has had response rates ranging from 40% to 50%, with approximately 30% of responders achieving remission [18,58]. However, sustaining these beneficial outcomes presents a challenge. While one study reported a response rate of 43.6% at 1 year after rTMS treatment [59], another study observed a response of merely 22.6% at 6 months after rTMS treatment [21]. A common strategy to sustain these positive effects is to provide maintenance rTMS [60,61]. However, maintained rTMS in depression has some disadvantages, such as being time-consuming; 37.8% of the patients relapsing within 20 weeks; and long-term treatment being linked to different side effects, including difficulty sleeping and headaches [62,63]. Therefore, a different strategy for relapse prevention after successful rTMS treatment is needed. PCT offers a relatively brief treatment course focused on relapse prevention in patients with MDD, with demonstrated long-term efficacy [22,33-37]. In this pilot study, we will offer PCT either face-to-face or online to patients who have recently effectively finished rTMS treatment to establish the feasibility of the different delivery formats for a larger RCT on the efficacy of administering PCT after rTMS. To our knowledge, this is the first study to provide PCT immediately following rTMS. Other strengths of this study include the extensive measurement of treatment adherence and daily measurement of affect as earlier research has established fluctuations in affect as predictors of depression relapse [7,8]. A limitation of this study is that it is single-blinded as the participants are aware of their group allocation. To minimize related bias within this study, a blinded outcome assessor will conduct all questionnaires, and participants are instructed not to tell this assessor their treatment allocation.

In conclusion, the findings of this pilot study may enhance our means to study an add-on treatment strategy for promoting remission as well as relapse prevention in patients with MDD after successful rTMS treatment and likely increase treatment adherence in an RCT on the effectiveness of PCT following rTMS treatment as a prevention strategy.

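### The affect fluctuation outcome has a mean as its only score, and the planned model compares level and trend, so day-to-day fluctuation is not measured

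*Protocol article*

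**What the plan says.** The Objectives section sets out to explore the effects of offering PCT after rTMS "on affect fluctuations and remission periods, and study the potential benefits of these measurements for a larger trial". Secondary Outcomes names the construct: "Affect fluctuations are the second study parameter". It is measured by a short daily questionnaire with a visual analog mood scale and questions on positive and negative affect. The one derived quantity follows: "Participants will complete the daily questionnaire on their affective state during PCT, from which the mean affect score will be calculated".

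The Background justifies the measurement by research in which "fluctuations in positive and negative affect, especially reductions in positive affect, can predict depressive symptomatology up to 6 months after remission". The Discussion lists daily affect measurement as a strength because "earlier research has established fluctuations in affect as predictors of depression relapse".

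Statistical Analysis of the Secondary Objectives says: "Repeated linear mixed models will be used if normality is reached to compare variation in" individual affect over time in the two groups. Participant enters as a random intercept, with sex and age as possible covariates. No other random effect and no residual structure is described. The section adds that descriptive results of the secondary parameters will be illustrated qualitatively.

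**The concern.** Three things should line up here: the construct named (fluctuation), the score derived (a mean) and the model fitted (a random-intercept linear mixed model). The second and third describe how high affect is and how it drifts. Neither describes how much a person varies from one day to the next.

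The Abstract says the experience sampling data are meant to establish usefulness for a larger trial. If the report shows no difference in mean affect or its trend under a fluctuation label, readers may conclude that fluctuation does not differ between formats, or is not worth measuring, when it was never estimated. Participants are asked for about 40 ratings each, and those ratings would support a direct measure.

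**Working it through.** The article gives no effect size, variance, alpha or power for this outcome, so there is no planned figure to reproduce. The check is a comparison of definitions, an algebraic step and an illustration on assumed values.

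**Inputs from the article**
- Ratings: 5 a week (Table 1) over 8 weekly sessions (Study Design), so 5 × 8 = 40 per person. Table 1 gives 60 minutes in total, and 60 / 40 = 1.5 minutes each, which is consistent.
- Sample: 20 planned at 1:1; 11 included (Results).
- Score: a mean, averaging unit not stated. Model: participant random intercept only.

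**What each reading of the mean leaves**
- Mean over the whole PCT period: one number per person, and variability is gone. A repeated-measures model could not be fitted to it.
- Mean over items within each questionnaire: the daily series survives. The model can be fitted, but its fixed effects are level and trend. Day-to-day spread goes into the residual, which by common default is shared by all participants. The article does not state this either way.

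On neither reading is a fluctuation quantity defined.

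**Why a mean does not register fluctuation**

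Let person i in arm g have between-person SD τ, within-person SD σ_g and n independent daily ratings. The expected person mean is the arm mean, whatever σ_g is. Its variance is τ² + σ_g²/n. With assumed τ = 10 and n = 40:
- σ = 10: 100 + 100/40 = 102.5, SD 10.12
- σ = 20: 100 + 400/40 = 110, SD 10.49

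Doubling the within-person SD leaves the expected mean unchanged and widens the spread of person means by 10.49 / 10.12 = 1.04. By contrast, the expected squared successive difference is 2σ². The RMSSD (root mean square of successive differences) is then about √200 = 14.1 against √800 = 28.3, a log difference of ln 2 = 0.69.

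**Simulation** (assumed: equal arm means, τ = 10, within-person SD 10 in one arm and up to 20 in the other, independent days, two-sided 5% tests)
- t test on the person mean: rejects in 4 to 6% of runs, even at SD 10 versus 20.
- t test on the person slope: 4 to 6%.
- Random-intercept mixed model, 10 per arm, 40 days, SD 10 versus 20, 200 runs: 6.5% for group and 4.5% for group by time. The Monte Carlo standard error is √(0.05 × 0.95 / 200) = 1.5 percentage points, so both agree with 5%. Some model fits gave convergence warnings; the person-mean and person-slope tests, which need no such fitting, agree with them.

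| t test on log RMSSD | SD 10 vs 12 | 10 vs 15 | 10 vs 20 |
|---|---|---|---|
| 10 per arm, 40 days | 80% | about 100% | about 100% |
| 5 per arm, 40 days | 46% | 98% | 100% |
| 5 per arm, 20 days | 22% | 79% | nearly 100% |

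Under harder assumptions (lag-1 correlation 0.3, within-person SD varying 25% between people, 40 ratings, log within-person SD as the score), a ratio of 1.5 is detected in 87% of runs with 10 versus 10 and 58% with 6 versus 5. The detection rates therefore depend heavily on what is assumed. The roughly 5% rate for level-based summaries follows from building in equal means.

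**The case against.** A reader might infer that the plan throws the fluctuation information away and cannot answer its secondary objective at all. The article does not support that, for four reasons.

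- The averaging unit is unstated. Because the questionnaire has several items, a mean over items per questionnaire is an ordinary reading. A repeated model over time only makes sense if the daily series is kept.
- The article uses fluctuation loosely. The Abstract speaks of changes in affective states, and the Background stresses reductions in positive affect, which are changes in level. On that usage, a model of daily affect over time answers part of the objective.
- A single residual variance is a software default, not something the article states. A fuller analysis plan, not shown here, could specify otherwise.
- The qualitative description of secondary parameters could show variability informally.

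The simulation is also close to circular, since a test of means must sit at its nominal level when the means are set equal. Its variance ratios appear nowhere in the article.

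All of this stands, and it limits the claim. It does not remove the mismatch. The article does not simply leave the score to another document; it names one, and the one it names measures level. Even on the most generous reading, nothing in the text yields an estimate of within-person variability.

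**Conclusion.** The point holds as a mismatch between outcome name, score and model. Followed as written, the plan gives affect level and its trend by format, and no measure of day-to-day fluctuation. Where fluctuation means change in level over time, the model serves that part of the objective and no more.

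This conclusion rests on the text and the algebra, not on the simulated percentages, which are illustrative because the article gives no effect size or variance.

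The weight is moderate. The outcome is secondary, in a pilot with 11 participants, and neither adherence nor the 75% completion criterion depends on it. It is worth correcting because the measurement is meant to inform a larger trial and because, as of June 2026, analysis had not begun.

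**What to change.** **In Secondary Outcomes:**
1. State that the mean is taken over items within each completed questionnaire, separately for positive and negative affect, so that the daily series is kept.
2. Add one prespecified within-person variability score per participant, for each of the two scales. Options are the SD around the person's own linear trend, or the RMSSD restricted to consecutive rating days. Choose one.
3. Keep mean affect level and trend as a separate, separately named outcome.

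**In Statistical Analysis of the Secondary Objectives:** report the variability score by format on the log scale, as a ratio with a confidence interval, labelled exploratory. The mixed model stays for level and trend. A location-scale model is not needed with 11 participants.

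**Cost:** a few lines of analysis on data already collected, and a dated change made before the affect data are examined. If analysis has started since June 2026, the report should say so.

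**Limits to state:**
- Scores are noisy for participants with few ratings, so report the number of ratings or weight by it.
- With five fixed days a week, RMSSD loses pairs. Five adjacent days give 4 consecutive pairs a week (4 × 8 = 32); two separate rest days give 3 (3 × 8 = 24).
- The estimate will be imprecise. Assume a 6 and 5 split, 40 independent ratings each and 25% between-person variation in SD. The variance of a log SD is then about 0.25² + 1/(2 × 39) = 0.0753, or SD 0.274. The standard error of the difference is 0.274 × √(1/6 + 1/5) = 0.166. With t = 2.262 on 9 degrees of freedom, the 95% interval is ±0.376, a factor of about 1.46 either way.
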